### Ethical issues

The protocols and procedures of the PRONAF study were in agreement with the ethical guidelines on biomedical research on human subjects of the World Medical Association’s Declaration of Helsinki (1964) and further amendments. Before participating in this research, all subjects were carefully informed about the possible risks and benefits of the project, being required to read and sign an institutionally approved informed consent document. PRONAF study was approved by the Human Research Review Committee of the University Hospital La Paz (PI-643).

Access to the database was restricted to the researchers that participated in the PRONAF study. Therefore, the data and information obtained in the project was considered as confidential following current Spanish legislation regulating personal data protection (Organic Law 15/1999 and Royal Decree 1720/2007).

This trial was registered at clinical trials.gov as NCT01116856. http://clinicaltrials.gov/.

### Intervention

#### Time line intervention

The assessments took place for all subjects one week before and after 22 weeks of intervention. Additionally, body weight was measured every 15 days, training intensity and physical activity were controlled monthly, and dietary intake was evaluated every three months.

#### Exercise protocols

Four different intervention groups were involved in the study as stated above. The S, E and SE groups followed the corresponding training program plus the dietary intervention, and the C group followed the dietary intervention and was instructed about the general recommendations regarding physical activity for weight loss from the American College of Sports Medicine (ACSM) [44].

Subjects in the S, E and SE groups performed training 3 times/wk for 22 weeks at a Sports Centre in Madrid (Spain). All training sessions were carefully supervised by certified personal trainers. The exercise programs were designed taking into account each subject’s muscle strength (MS) and the heart rate reserve (HRR). MS was measured using the 15-repetition maximum (15 RM) testing method [45] in the S and SE groups (both of which involved strength training). Both volume and intensity of exercise was increased over the study period (Figure 2) according to standard procedures [35,41].

**Figure 2 F2:**
[figure not shown]
**Time line of the Study.** S, strength training group; E, endurance training group; SE, combined strength plus endurance training group; C, physical activity recommendations group.

Prior to each training session each subject started with a 5-minute aerobic warm-up routine, followed by the session routine, and concluded with a 5-minute cool down and stretching exercises routine. Moreover, an MP3 audio track was played for each participant to set the execution rhythm of the exercises during all the sessions. In this case, the heart rate (HR) was monitored by a pulse-meter (Polar RS800CX, Polar Electro, Kempele, Finland). The cadence for the resistance exercises was fixed at 1:2 (concentric-eccentric phase). A session routine consisted in the execution on eight scheduled exercises in the case of group S (i.e., shoulder press, squat, barbell row, lateral split, bench press, front split, biceps curl and French press for triceps). Regarding types of exercises, running, cycling or elliptical (self-selected) exercises were the main components of the session routine for group E, while the routine for the SE group consisted in a combination of cycle ergometry, treadmill or elliptical intercalated with squat, row machine, bench press and front split.

The volume and intensity of the three training programs increased progressively. During the adaptation period (cf. weeks 1–4) subjects were taught on the exercise technique. Between the fifth and eight week, exercises were carried out at an intensity of 50% of 15RM and HRR, performing 2 laps to the circuit (cf. 51 minutes and 15 seconds), then between the 9^th^ and 14^th^ week the intensity was increased up to 60% of 15RM and HRR, and finally during the period between the 15^th^ and 24^th^ week the volume increased from 2 to 3 laps to the circuit (64 minutes). Then, a five-minute recovery period was set between the circuits. The S and SE participants performed 15 repetitions (45”) for each exercise with a rest period of 15 seconds between them.

#### Diet intervention

Hypocaloric diets (between 5028 and 12570 KJ) were prescribed individually for all participants by expert dieticians at the Department of Nutrition, La Paz University Hospital, Madrid. The diet was designed to provide 25-30% less energy than the daily energy expenditure (DEE), as measured using SenseWear Pro3 Armband™ (Body Media, Pittsburgh, PA). Approximately, 29–34% of the energy came from fat, 14–18% from protein, and 50–55% from carbohydrates [46]. In the obesity group, energy provided from protein was increased up to 14–20%.

### Before-after measurements

#### Physical fitness and health

##### Maximal aerobic power test

The test was conducted on a computerized treadmill (H/P/COSMOS 3P^®^ 4.0, H/P/Cosmos Sports & Medical, Nussdorf-Traunstein, Germany). Peak oxygen uptake (VO_2_ peak) was measured with the modified Bruce protocol used elsewhere with overweight and obese population [35,47]. Volume and composition of expired gas was analysed with a gas analyzer Jaeger Oxycon Pro (Erich Jaeger, Viasys Healthcare, Germany) which validity and reliability has been demonstrated previously [48,49], and continuous 12-lead electrocardiographic monitoring. The exercise test was maintained until exhaustion. The mean of the three highest measurements was used as VO_2_ peak. Identical procedure was carried out to calculate the maximal HR.

#### Resting metabolic rate

Subjects were asked to refrain from any exercise for at least 24 h before the test. To assess the resting metabolic rate (RMR), participants were cited between 7 am to 10 am, after a 9 h overnight fasted period. RMR was then measured by indirect calorimetry standing up (during 11 min) and in a lying position (additional 20 min). Oxygen uptake (VO_2_) and carbon dioxide production (VCO_2_) were recorded by a gas analyzer Jaeger Oxycon Pro (Erich Jaeger, Viasys Healthcare, Germany), and resting heart rate (RHR) was measured using a heart rate monitor (Polar Electro Oy, Kempele, Finland). All these parameters were averaged during the last 5 min of the standing up position and the last 10 min of the lying position. Oxigen uptake and VCO_2_ data were used to calculate RMR according to the formula of Weir [50].

#### Maximal dynamic strength

Muscle strength was measured with the 15RM testing method described elsewhere [51] for both strength training groups S and SE. The 15 RM for each exercise was tested twice on different days during the evaluation periods. The intraclass correlation coefficient of reliability for all the exercises was ICCr = 0,995 and ICCr = 0,994 for men and women, respectively. All the assessments, the data collection sessions and the previous trainings were carried out with the same machines and free weights (Johnson Health Tech. Iberica, Matrix, Spain).

#### Static strength (dinamometry)

The general strength index (SI) was calculated using previous criteria [52]. This method measures leg and arm strength with respect to body weight via two exercises: the bench press and squat. The dynamometric strength index (DSI) was calculated by measuring muscular strength using a Tecsymp Tkk5002 hand dynamometer and a Tecsymp Tkk5401 leg and back dynamometer (Tecsymp, Barcelona, Spain). The DSI value was calculated as the sum of the values obtained with both apparatuses divided by subject’s body weight.

#### Physical activity and daily energy expenditure

Habitual physical activity (PA) was assessed with a SenseWear Pro3 Armband™ (Body Media, Pittsburgh, PA). Subjects were instructed to wear the monitor continuously for 5 days including weekend days and weekdays following general recommendations [53]. Data was recorded by 15 min intervals. DEE was calculated using the Body Media propriety algorithm (Innerview Research Software Version 6.0).

#### Energy balance, adherence to diet and exercise

All subjects were instructed to continue their habitual daily activities as before the intervention period. They were required to report the kind, duration, and intensity of any physical activity and the amount of any food undertaken during the intervention period.

At the beginning of the intervention, negative energy balance was calculated taking into account the DEE, and a 3-day food record, in order to decrease the energy intake of the diet by a 25-30% during the intervention.

In one hand, adherence to diet was calculated as the estimated Kcal of the diet divided by the real Kcal intake in percentage ([estimated kcal of diet/real Kcal intake] · 100), representing the highest adherence the value 100%. Higher values mean a higher restriction and viceversa. On the other hand, adherence to exercise was calculated by the number of sessions completed in regard to the theoretical sessions ([sessions performed /total sessions] · 100).

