### Inclusion and exclusion criteria

Inclusion criteria included being male or female living in the Region of Madrid, being overweight (BMI 25–29.9 kg/m^2^) or obese (BMI: 30–34.9 kg/m^2^), middle-aged (from 18 to 50 years), having a sedentary lifestyles (< 30 min Physical Activity/day), being normoglycaemic, and non-smoker [37,41]. In the case of females, having regular menstrual cycles was required.

The exclusion criteria were suffering from a physical (orthopaedic limitations, stroke, etc.) and/or psychological (anorexia, bulimia, etc.) disease that may have precluded the performance of the requested strength or endurance training, intake of any medication (beta blockers, alcohol, etc.) known to influence physical performance or the interpretation of the results, having a history of systematic strength or endurance training (moderate to high intensity training more than once a week) in the year before the beginning of the study [37,40].

After the intervention period, participants who failed to comply with 90% assistance to the training sessions and less than 80% adherence to the diet were excluded from further analysis. The characteristics of the final sample (completers) are shown in Table 1.

**Table 1 T1:** Baseline data (n = 180)

	**Overweight n = 84**		**Obesity n = 96**	
	**Women**	**Men**	**Women**	**Men**
	**n = 48**	**n = 36**	**n = 48**	**n = 48**
Age (years)	37.29 ± 8.25	37.42 ± 8.02	39.02 ± 7.74	38.79 ± 7.99
Body Weight (kg)	73.5 ± 5.87	88.21 ± 8.13	88.33 ± 10.1	102.04 ± 8.94
Height (m)	1.62 ± 0.06	1.75 ± 0.07	1.64 ± 0.07	1.77 ± 0.06
BMI (kg/m^2^)	28.01 ± 1.32	28.57 ± 1.12	32.41 ± 1.85	32.4 ± 1.9
Body fat (%)	43.28 ± 3.62	33.8 ± 4.63	47.11 ± 3.49	38.17 ± 4.02
Body fat free mass (kg)	40.25 ± 4.3	55.99 ± 5.47	44.3 ± 4.71	58.63 ± 8.96
Bone mineral density (g/cm^2^)	1.18 ± 0.1	1.26 ± 0.09	1.21 ± 0.11	1.3 ± 0.1

Results are shown as Mean ± SD.

*Note*. BMI = Body Mass Index. Body fat, Body fat free mass and Bone mineral density calculated by Dual-energy x-ray absorptiometry (DXA).

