##### Eating behaviour

At baseline and at the end of the intervention all food and beverages consumed by the participants were recorded using a food frequency questionnaire and a “3-day food and drink record”, validated for the Spanish population [57]. This recorded all food and drinks consumed at home and away for three days, including 2 weekdays and 1 weekend day. Subjects were instructed to record the weights of food consumed if possible and to use household measurements (spoonfuls, cups, etc.) if not. The energy and nutritional content of the food consumed was then calculated using the DIAL software (Alce Ingeniería, 2004). Then, the values obtained were compared to the recommended dietary intakes for the Spanish population to determine dietary adequacy [58].

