#### Dietary intake control

A dietician interviewed each participant at baseline, and at 3 and 6 months after the start of the intervention. All subjects were instructed about how to record their dietary intake using a daily log, and given recommended portion sizes and information on possible food swaps. In addition, voluntary group nutrition education sessions were given by the dieticians. The goal was to equip the participants with the necessary knowledge and skills to achieve gradual, permanent behavioural changes.

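### The diet-adherence score has no upper limit and the 80% exclusion works on one side only, so recorded over-eating can fail the diet criterion but recorded under-eating never can

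*Protocol article*

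**What the plan says.** In the protocol article, section *Energy balance, adherence to diet and exercise*, "adherence to diet was calculated as the estimated Kcal of the diet divided by the real Kcal intake in percentage". The same sentence goes on to interpret the score: "representing the highest adherence the value 100%. Higher values mean a higher restriction and viceversa".

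The section *Inclusion and exclusion criteria* then uses the score to select the analysed sample: "participants who failed to comply with 90% assistance to the training sessions and less than 80% adherence to the diet were excluded from further analysis". It gives no upper limit. Table 1, with 180 participants, is presented as the sample left after this step.

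Intake comes from the participants themselves. During the intervention, "They were required to report the kind, duration, and intensity of any physical activity and the amount of any food undertaken during the intervention period", and under *Dietary intake control*, "All subjects were instructed about how to record their dietary intake using a daily log". At baseline and at the end, "all food and beverages consumed by the participants were recorded using a food frequency questionnaire" together with a three-day record (*Eating behaviour*).

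**The concern.** The two sections do not fit together. If 100% is the best value, a departure in either direction is worse adherence, yet the exclusion acts on one direction only. If a higher value is better, 100% is not the highest, and a participant who records half the prescribed energy outranks one who follows the prescription.

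This matters because the score helps to decide who is analysed. It is observed after randomisation and is closely tied to weight and fat change, and body fat percentage is the variable on which the trial was sized. Removing participants from one tail of such a variable is selection on something near the outcome. All four arms follow the dietary intervention, so the comparison of exercise programmes relies on dietary restriction being similar across arms. A rule that trims only recorded over-eaters could disturb that balance.

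**Working it through.** The article states no figure for this point that could be reproduced. The check is arithmetic on its own formula.

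**Inputs.** Score A = 100 × prescribed / recorded intake (*Energy balance, adherence to diet and exercise*). Diet criterion failed if A < 80 (*Inclusion and exclusion criteria*). Prescription 25–30% below daily energy expenditure, DEE (*Diet intervention*). Six of 59 losses attributed to low diet adherence, 239 starters, 180 completers (*Population and sample size estimation*).

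**1. What the floor means.** A < 80 is the same as recorded intake > 1/0.80 = 1.25 times the prescription.

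| Recorded intake, % of prescription | Score A | Diet criterion |
|---|---|---|
| 50 | 200 | passes |
| 80 | 125 | passes |
| 100 | 100 | passes |
| 125 | 80.0 | passes |
| 126 | 79.4 | fails |
| 150 | 66.7 | fails |

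No recorded intake below the prescription, however low, can fail.

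**2. The floor against the intended deficit.** The prescription is 70–75% of DEE. At the cut-off, intake is 1.25 × 0.70 = 0.875 to 1.25 × 0.75 = 0.9375 of DEE. The remaining deficit is 12.5% or 6.25%, against an intended 30% or 25%.

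**3. Effect of self-recording.** If a fraction u of intake goes unrecorded and true intake is t times the prescription, A = 100 / [t(1 − u)]. The documents give no value for u, so this is an assumed range. For t = 1.40 the score is 71.4 with full recording, 79.4 at u = 10%, 89.3 at 20% and 102.0 at 30%. The highest true intake that still passes is 1.25/(1 − u): 139%, 156% and 179% of the prescription at 10%, 20% and 30%.

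**4. How many people the floor can have removed.** The listed reasons add up: 17 + 3 + 6 + 6 + 27 = 59, and 239 − 59 = 180, the Table 1 sample. Exclusions for diet therefore lie within the 59, and the category that names diet has 6: 6/239 = 2.5%.

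**5. A rough size.** Assume that these six lost no weight at all and that arms are pooled. Restoring them multiplies the mean loss by 180/186 = 0.968, so the completers' mean is overstated by 186/180 − 1 = 3.3%. As an extreme, take 180/4 = 45 completers per arm on average and put all six in one arm: 51/45 − 1 = 13% in that arm. The article does not report the six by arm.

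**6. The joining word.** The exclusion sentence links attendance and diet with *and*. Read literally, a participant must fail both, so someone at 79.4 on diet with full attendance stays in. Read as two separate criteria, that person goes. *Exercise protocols* describes supervised sessions for S, E and SE only, so the reading chosen also affects how the rule applies to group C.

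**The case against.** The text does not treat over-restriction as full adherence. It sets 100% as the target and labels values above it as more restriction, which can be read as a target-centred scale that keeps the direction of departure. This stands. A reader might infer that eating too little is formally scored as perfect adherence; the article does not say so. What it does is let such participants pass the exclusion rule, since the 80% is attached to the score with no word about closeness to 100%.

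The numbers are small, and *Discussion* reports no difference between groups in the number of dropouts. This also stands and limits the size, although that statement covers all reasons together. The same diet rule applies in every arm, so the between-arm comparison is biased only if trimming or over-restriction differs by arm, and nothing in the article shows that it does.

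Under-recording affects any intake-based score, and a two-sided score would not cure it: someone truly at 125% who records 100% would score 100. The figures in step 3 therefore show sensitivity and are not evidence that participants in energy surplus were retained.

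A reader might also infer that scores above 100 hide non-adherence in reported averages. No section says that adherence is averaged by arm, so that inference has no support.

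Finally, there are dietician interviews, fortnightly weights, monthly activity monitoring and an outlier check, and a protocol book that is not shown may hold more. These are useful controls, but none of them alters the stated exclusion rule.

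**Conclusion.** The point holds as an inconsistency in a stated rule: 100% is called the highest adherence, the score has no ceiling, and the exclusion has only a floor. On the diet criterion, only recorded intake above 125% of the prescription fails.

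The rule *can* inflate apparent weight and fat loss and *can* bias the arm comparison. The stronger statement, that it does exaggerate the loss, is not supported. Removing recorded over-eaters pushes the estimate up, retained under-recorders pull it down, and the article gives neither the number scoring above 100 nor the exclusions by arm. The likely size is small: 2.5% of starters, and about 3% of the pooled mean loss if all six lost nothing. This rests on the six being the only participants removed for diet, and on their not being concentrated in one arm.

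**What to change.** - Reconcile the two sections so that adherence is measured as departure from 100% in both directions. State the scale, because a 20% departure measured on intake (80–120% of prescription) is not the same as an inverted ratio limit (80–125%). Where any limit lies is for the trial's dietetic team and is not proposed here.
- Apply one rule to all arms, and say plainly whether failing diet alone, failing attendance alone, or only failing both leads to exclusion.
- Keep every participant with outcome data in the main analysis as randomised. Use adherence for description and for a secondary per-protocol analysis.
- Report by arm how many participants fall below the floor and how many score above 100.

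The change is still possible: *Statistical analysis* is written in the future tense, and effectiveness results are left to later publications. The cost is one variable recomputed from data already held, and some participants will change class in the secondary analysis. A two-sided score does not correct for under-recording, and the report should say so.

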#### Psychological and eating behavior assessment

##### Quality of life

The impact of overweight and non-morbid obesity on Health-Related Quality of Life (HRQL) was assessed using two different questionnaires:

#### EUROQOL 5D (EQ-5D)

The EQ-5D, is a self-administered questionnaire capable of generating a score reflecting a value associated with a given health status. The EQ-5D™ descriptive system consists of five dimensions: 1. Mobility; 2. Self-care; 3. Usual activities; 4. Pain/discomfort; 5.Anxiety/depression. Each dimension has three levels: “level 1: no health problems”, “level 2: moderate health problems” and “level 3: extreme health problems”. Each unique health state described by the instrument has an associated 5-digit descriptor ranging from 11111 for perfect health to 33333 for the worst possible state. The resulting descriptive system defines 243 health states. The instrument also includes a 20-centimeter visual analogue scale for the self-assessment of current general health [54].

Short Form-36 Health Survey (SF-36) version 1.4, valid for the Spanish population was used [55]. This questionnaire evaluates the individual health status in two dimensions: functional and emotional. Functional status is divided in 6 subscales: Physical Functioning (PF), Role-Physical (RP), Bodily Pain (BP), Vitality (VT), Social Functioning (SF) and Role-Emotional (RE). Emotional status includes Mental Health (MH) and General Health (GH) subscales. Scores on all subscales range from 0 to 100 (higher scores indicate better health status) [56].

##### Eating behaviour

At baseline and at the end of the intervention all food and beverages consumed by the participants were recorded using a food frequency questionnaire and a “3-day food and drink record”, validated for the Spanish population [57]. This recorded all food and drinks consumed at home and away for three days, including 2 weekdays and 1 weekend day. Subjects were instructed to record the weights of food consumed if possible and to use household measurements (spoonfuls, cups, etc.) if not. The energy and nutritional content of the food consumed was then calculated using the DIAL software (Alce Ingeniería, 2004). Then, the values obtained were compared to the recommended dietary intakes for the Spanish population to determine dietary adequacy [58].

#### Body composition

##### Anthropometric measurements

Body height was measured using a SECA stadiometer (range 80-200 cm, Valencia, Spain). Body weight (BW) was measured using a TANITA BC-420MA balance (Bio Lógica Tecnología Médica S.L, Barcelona, Spain). BMI was calculated as [body weight (kg)/(height (m))2]. Waist circumference (WC) was measured using a SECA 201 steel tape (Quirumed, Valencia, Spain). Body fat percentage was measured using bioelectrical impedance analysis (BIA) with an OMRON BF 306^®^ analyzer (OMRON HEALTHCARE Co., Ltd, Ukyo-ku, Kyoto, Japan).

